### Sample size calculations

Stata V.13 was used for calculations. In order to obtain a result as precise as possible, we aimed to achieve the maximum feasible sample size. At the trial start in January 2015, there were 427 general practices active in CPRD. Based on previous experience,^18^ we estimated that it would be feasible to recruit a maximum of 120 CPRD general practices. The mean practice list size was 8537, and 120 general practices will include some 1.20 million registered patients, with about 224 000 RTI consultations over 12 months. Power calculations were computed based on primary outcome of antibiotic prescribing for RTI per 1000 participant-years, using data from the previous eCRT study.^18^ In the eCRT study, which included participants aged 18–59 years, the mean antibiotic prescribing rate for RTI was 112 per 1000 (SD 39.8). Therefore, for this study, based on the analysis of covariance, where participants of all ages will be included, including 60 GP practices in each trial arm, there will be more than 80% power, with two-sided α=0.05, to detect an absolute reduction in antibiotic prescription for RTI of 12 per 1000 registered patient years (or 1.2 per 100). If the SD is 25% larger, the study will still have 80% power to detect a reduction in antibiotic prescribing of 15 per 1000 (1.5 per 100 patients), or 17.5 per 1000 if the SD is 50% larger.

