### Allocation

The allocation will be performed at King's College London using anonymised practice identifiers passed from CPRD. The research team are at all times blind to the identity of trial practices, which is only known to CPRD staff. GP practices are allocated to intervention and control trial arms by minimisation controlling for baseline antibiotic prescribing quartile region (England, Scotland, Wales and Northern Ireland). Anonymised practice identifiers will then be returned to CPRD with trial arm allocation attached. This information will then be used to enable intervention activation at practices in the intervention trial arms. This procedure is considered to ensure adequate concealment throughout the allocation process.

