Trial analyses will be implemented using data aggregated to general practice level, using the family practice-specific rates or proportions as observations. This is the level for intended inferences. Effects of clinical and public health importance will be evident at this level. In general, a perfectly weighted cluster-level analysis will give similar precision as an individual-level analysis.^28^ Analyses for primary and secondary outcomes will estimate the difference (95% CI) in the outcome between intervention and control trial arms. Primary and secondary analyses will be adjusted for the preintervention value of the outcome, in an analysis of covariance framework, as well as proportion by age group and proportion of women at the practice. Minimum variance weights will be used to allow for varying numbers of participants and consultations per practice.^29^ Intervention usage (number of times prescribing reports or decision support tools are accessed) will be divided into quartiles and a trend tests implemented by introducing these into analyses as continuous variables. Data for healthcare usage and costs will be analysed at the individual level using a two-part model as reported previously.^30^ Given the extent of data available for analysis, we can readily evaluate shifts in practices' use of diagnostic categories, using pretrial data to evaluate time trends.

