#### Study status

The intervention development phase has been completed. Recruitment for the trail started in August 2015. The first batch of 19 practices was randomised in November 2015 and these practices acted as an internal pilot. Currently, 76 practices are part of the study.

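### Region is a minimisation factor but is absent from the stated ANCOVA covariates, so the analysis may be somewhat conservative

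*Protocol article*

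**What the plan says.** The Allocation section of the protocol article describes "minimisation controlling for baseline antibiotic prescribing quartile region (England, Scotland, Wales and Northern Ireland". A conjunction seems to have dropped out between quartile and region. I read the sentence as two factors, prescribing quartile and UK nation. If it meant quartile within nation, region would still be a balancing factor.

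The Outcome evaluation section then gives the adjustment set for the effectiveness analyses: "Primary and secondary analyses will be adjusted for the preintervention value of the outcome, in an analysis of covariance framework". Two further covariates are named there, the age mix of the practice and its share of women. The unit of analysis is the practice: "Trial analyses will be implemented using data aggregated to general practice level". No other section adds region to these models.

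The secondary outcomes include the RTI consultation rate and the proportion of RTI consultations that lead to an antibiotic. Each is adjusted for its own baseline, not for baseline antibiotic prescribing.

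**The concern.** Balancing the arms on a prognostic factor makes the treatment estimate less variable than it would be under simple randomisation. A model that leaves the factor out does not know this. It keeps the factor's variance in the residual and reports a standard error that is too large for the allocation actually used. Confidence intervals are then too wide, the test rejects less than 5% of the time under the null, and some power is given up.

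In the primary model, the continuous baseline value of the outcome largely carries one of the two balancing factors, prescribing quartile. Region has no such stand-in. In a model for the RTI consultation rate, neither balancing factor enters as such. With recruitment expected to reach at most 120 practices, precision is worth keeping.

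**Working it through.** **Inputs from the article (Sample size calculations).** The design is "including 60 GP practices in each trial arm", with mean 112 per 1000, SD 39.8, target reduction 12 per 1000 and "there will be more than 80% power, with two-sided α=0.05".

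**Step 1: the plan's own power.** The unadjusted SE of the difference is 39.8 × √(2/60) = 7.27. Power is Φ(12/7.27 − 1.96) = Φ(−0.31) = 37.9%. The stated figure therefore relies on the ANCOVA. With baseline–follow-up correlation r, the SD becomes 39.8 × √(1 − r²):

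- r = 0.80: power 78.6%
- r = 0.81: power 80.4%
- r = 0.82: power 82.3%

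The article does not state r. A value of about 0.82 is compatible with all three detectable differences it gives (12, 15 and 17.5 per 1000). The power claim makes no use of region.

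**Step 2: closed form for leaving region out.** Let R² be the share of residual variance, after the listed covariates, that region explains. With region balanced between arms:

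- ratio of model SE to true SE = 1/√(1 − R²)
- true type I error = 2 × [1 − Φ(1.96/√(1 − R²))]

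The article gives no R², so it is an assumption:

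- 2%: 1/√0.98 = 1.010; 1.96 × 1.010 = 1.980; type I error 4.8%
- 5%: 1/√0.95 = 1.026; 1.96 × 1.026 = 2.011; type I error 4.4%
- 10%: 1/√0.90 = 1.054; 1.96 × 1.054 = 2.066; type I error 3.9%

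**Step 3: simulation.** The set-up was 120 practices, minimisation on prescribing quartile and region, unweighted practice-level ANCOVA with and without region indicators, and 4000 runs per setting. Assumptions not in the article are r = 0.82, assignment probability 0.8, region shares of 60/20/12/8%, and omission of the age and sex covariates. Each cell shows without region → with region.

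| Assumed R² | Mean model SE | Type I error | Power for 12 per 1000 |
|---|---|---|---|
| 0% | 4.15 → 4.16 | 4.7% → 4.7% | 81.4% → 81.3% |
| 2% | 4.15 → 4.12 | 4.1% → 4.2% | 80.6% → 81.2% |
| 5% | 4.16 → 4.06 | 4.3% → 5.0% | 82.1% → 82.8% |
| 10% | 4.16 → 3.95 | 4.0% → 4.7% | 82.2% → 84.6% |
| 20% | 4.16 → 3.72 | 2.8% → 4.6% | 82.6% → 88.0% |
| 30% | 4.16 → 3.49 | 2.7% → 5.4% | 84.0% → 91.8% |

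Monte Carlo error is about √(0.05 × 0.95/4000) = 0.3 points on the type I error and √(0.82 × 0.18/4000) = 0.6 points on power, so the 2% row shows no clear difference in either.

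At 10% under the null, the actual spread of the estimate is 3.97 without region and 3.94 with it, against model SEs of 4.16 and 3.95. Minimisation has already delivered the precision; the model without region fails to report it.

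**The case against.** **The baseline value may absorb most of region.** A stable difference between nations in prescribing is largely carried by the practice's own rate in the previous 12 months. At r = 0.82 that covariate removes 0.82² = 67% of the variance. What remains for region is change specific to a nation, or whatever the baseline misses. This stands, and it is why the harm is conditional. The article does expect local and national prescribing initiatives during the trial (Strengths and limitations; Process evaluation). An initiative that began in one nation during follow-up would escape the baseline, but that is an inference without a figure behind it.

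**The covariate list may be completed in an SAP that is not shown.** That is possible. But the article does not leave the adjustment set open: it names particular covariates, and the named set departs from the stated allocation.

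**Region is not entirely free.** It uses 3 degrees of freedom, some nations may contribute few practices, and the Study status section reports 76 practices so far rather than 120. This stands, but at R² = 0 with 120 practices the simulated loss is 0.1 point of power.

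**The secondary-outcome part has no size attached.** Each outcome's own baseline is normally its strongest predictor, and nothing shows how much baseline prescribing would add. This stands. The point is only that a balancing factor is missing.

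**Stronger readings that the article does not support:**

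- A reader might infer that the pilot batch also belongs in the model, since "The first batch of 19 practices was randomised in November 2015 and these practices acted as an internal pilot". Batch is not named as a minimisation factor, so the argument about balancing and then ignoring a factor does not extend to it.
- A reader might infer that region is missing from every analysis. The article lists no covariates for the cost models and states no model for the safety comparisons, so the point is limited to the primary and secondary ANCOVA models.

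**Conclusion.** The mismatch between allocation and analysis is real: region is balanced on and then left out of the stated ANCOVA covariates. For secondary outcomes whose own baseline is something else, baseline antibiotic prescribing is left out too.

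The consequence is conditional and conservative. If region explains 2% to 10% of the variance left after the baseline value, age and sex, the SE is overstated by about 1.0% to 5.4% and the type I error is about 4.8% to 3.9%. In the simulation, adding region gains under 1 point of power at 5% and about 2.4 points at 10%. If region explains nothing further, there is nothing to gain. These shares are assumptions, because the article gives no regional variance.

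It would be tempting to conclude that the standard errors are definitely wrong, that the result is biased, or that the power claim fails. None of these follows. The first depends on an unknown R². The estimate is unbiased with or without region. Simulated power without region stayed above 80% at every share tried, given r = 0.82 and 120 practices. The change is worth making because it is cheap, not because validity is threatened.

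**What to change.** 1. Add region (the four UK nations) to the ANCOVA models for the primary and all secondary outcomes. Fix in advance a rule for merging nations with very few practices, so that the choice does not depend on outcome data.
2. Add the baseline antibiotic prescribing rate to each secondary-outcome model in which it is not already that outcome's own baseline.
3. If region is to stay out, state the reason before outcome data are analysed.

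The cost is a change of analysis wording and about 3 degrees of freedom for region, or 4 where baseline prescribing is also added. Both variables are already held for the minimisation.

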### Process evaluation

A process evaluation will be conducted to evaluate the barriers and facilitators to implementation and the use of the intervention using a mixed-methods approach. Participants in the process evaluation will primarily include GPs, but staff involved with intervention implementation will also be included, aiming pragmatically for the maximum achievable sample. We will aim to recruit practitioners with a range of experiences of the intervention to explore their unique and important perspective. A questionnaire and an interview guide will be developed guided by criteria suggested by Linnan and Steckler^31^ for the process evaluation of public health interventions and research and will explore participants' experiences of using the intervention materials and experiences of the study implementation. Inductive thematic analysis will be used to analyse qualitative data. As a part of process evaluation, contextual information on initiatives to influence antibiotic prescribing, which might be implemented both locally and nationally, will be collected. This will include periodic surveys of documentary sources, primarily those accessible on the internet. It will also include specific questionnaire items concerning participating practices' exposure to other influences, such as interaction with the local National Health Service (NHS) prescribing advisers. As a part of process evaluation, compliance with the intervention protocol will be assessed. This will be done by evaluating the total number of times the intervention tools (including the practice prescribing reports, the decision support tools and webinars) are accessed over the intervention period.

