### Intervention development and implementation

The development of the intervention was informed by existing health records, behaviour change theory, systematic review evidence, clinical guidelines, qualitative research with non-trial practices (31 GPs and 3 nurse prescribers interviewed), as well as process evaluation data from the previous proof-of-concept trial.^25^ Main elements used in the previous eCRT study were refined and new elements were added. Two novel major components are the provision of practice-level feedback on antibiotic prescribing and recruitment of a GP champion for each practice since facilitation plays an important role affecting the context in which change occurs.^26^ A large part of the intervention refinement focused on the investigation of factors influencing implementation and selection of modifications of the tools in order to achieve maximum benefits of the intervention.

Practices in the intervention arm will receive complex multicomponent interventions, delivered remotely, which will include a 6 min web-based training webinar to promote effective usage of the intervention materials; prescribing support tools which will appear on intervention family practitioners' screens during consultations for specific RTI; monthly feedback on practice antibiotic prescribing in the preceding month from EHR analysis. Control practices will continue with usual care. The intervention will continue for 12 months. A detailed description of the development and design of the electronic prompts has been reported elsewhere^27^ and will be updated for this study.

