In order to preserve practices' anonymity, general practice recruitment will be conducted through the offices of CPRD. To ensure that an adequate practice recruitment and enrolment is achieved, regular meetings will be held with CPRD and Trial Steering Committee (TSC) overlooking the recruitment process. All CPRD general practices that are located in areas where research governance approvals have been obtained will receive an invitation pack, including a letter, consent form and information sheet. CPRD general practices that give informed consent to the study will be included in the trial. Intervention tools will be installed onto family practice information systems remotely as an add-on to existing software (DXS-Point-Of-Care). At the beginning of the intervention, GPs and nurse prescribers at intervention practices will be encouraged to watch a 6 min video narrated by a practising GP which aims to present the study and promote its effective usage. Once the tools become available on the practice system, a pop-up banner would appear after the first log-in to inform the doctor/nurse that the study tools are available on their system. During consultations for RTIs, electronic prompts will be activated by the entry of specific Read codes related to RTIs. Healthcare professionals will see the prompts in the right bottom corner of their screen and these prompts would offer two options to select: an option to print out a patient information leaflet or an option to check whether a patient is among a group of patients who are likely to be at risk of developing complications. Five condition-specific leaflets are available for adults (for common cold, sore throat, cough and bronchitis, sinusitis and otitis media). There are also two separate leaflets for parents of children who present with cough or middle ear infection. The leaflets give patients information on realistic recovery times, self-management strategies, explain why antibiotics are not needed, inform about the modest benefits and potential harms from antibiotic treatment, list serious signs of when patients should seek medical help and provide patients with clear guidelines as to when they should reconsult if their symptoms do not improve. These prompts aim to help GPs follow the guideline behaviour. The main focus is to encourage GPs not to prescribe antibiotics rather than to prescribe an antibiotic or offer a delayed prescription. All management decisions for individual patients remain at the discretion of individual GPs. Each practice in the intervention arm will also receive monthly feedback on their antibiotic prescribing in the preceding month from CPRD analysis. The reports would present the prescribing rates in a table format and would also include evidence for safe best practice in RTIs management. Practices will be encouraged to review the monthly feedback received as part of the trial during practice meetings. GP champion for each practice will be encouraged to circulate the feedback prior to the meeting and ensure that the discussion of the feedback is on the meeting agenda.

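### Intervention usage is defined as a pooled access count, which cannot show whether prescribing feedback was taken up or relates to prescribing

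*Protocol article*

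**What the plan says.** Two sections of the protocol article define how much of the intervention a practice received.

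- **Process evaluation.** Compliance is assessed by "evaluating the total number of times the intervention tools (including the practice prescribing reports, the decision support tools and webinars) are accessed". Three components go into one 12-month total.
- **Outcome evaluation.** "Intervention usage (number of times prescribing reports or decision support tools are accessed) will be divided into quartiles", with a trend test to follow. Webinars are not listed here. Quartiles of usage are also named among the secondary outcomes.

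Other sections show what the measure needs to capture. The Abstract states that the research will specifically evaluate feeding EHR data back to practices. Intervention development and implementation says: "Two novel major components are the provision of practice-level feedback on antibiotic prescribing and recruitment of a GP champion for each practice". The same section provides for one report a month over a 12-month intervention, and for prompts triggered when particular RTI Read codes are entered. It adds that the "GP champion for each practice will be encouraged to circulate the feedback prior to the meeting".

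**The concern.** The components offer very different numbers of occasions for access. A prompt can appear at any suitably coded RTI consultation, whereas a report arrives once a month. When such counts are added, the sum tends to rank practices by the more frequent component, and the reader cannot tell how much either contributed.

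Feedback is one of the two features that distinguish this trial from the earlier eCRT trial, which tested decision support tools alone. If usage is analysed as a sum, a rising or flat trend across quartiles may be read as evidence about the whole package when it mainly reflects one part. A practice that opened every report but rarely used the prompts, and one that did the reverse, can land in any order. The compliance figure has the same weakness: a high total does not show that any report was opened.

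**Working it through.** **Inputs from the document**

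- Sample size calculations: about 224,000 "RTI consultations over 12 months" in 120 practices, "including 60 GP practices in each trial arm". Usage exists only in the 60 intervention practices.
- Intervention development and implementation: monthly reports for 12 months, so 12 issued per practice.
- No access rate for prompts or reports is stated. The Background says only that many GPs underused the tools in the earlier trial.

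**Step 1: opportunities per practice-year**

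224,000 / 120 = 1,867 RTI consultations.

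The same paragraph is not internally consistent on list size: "The mean practice list size was 8537", and 8,537 × 120 = 1,024,440, yet "120 general practices will include some 1.20 million registered patients". If 224,000 was derived from 1.20 million patients, the implied rate is 224,000 / 1,200,000 = 186.7 per 1,000. A practice of 8,537 would then have 0.1867 × 8,537 = 1,594 consultations.

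The ratio of prompt opportunities to reports issued is therefore 1,594/12 = 133 to 1,867/12 = 156. These are opportunities and issued reports, not accesses.

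**Step 2: share of the total that comes from reports**

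Share = R / (R + u × 1,867), where R is report accesses per practice-year and u is assumed tool accesses per RTI consultation. If every report is opened, R = 12 with one reader per report and R = 60 with five.

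| u | R = 12 | R = 60 |
|---|---|---|
| 100% | 0.6% | 3% |
| 10% | 6% | 24% |
| 5% | 11% | 39% |
| 2% | 24% | 62% |
| 1% | 39% | 76% |

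**Step 3: does the total rank practices by report use?**

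Simulation of 60 practices, at least 500 replicates per setting. Assumptions: prompt accesses binomial with mean rate u varying between practices; lognormal practice size (log-scale SD 0.5); report accesses out of 12 × readers, with a practice-specific opening probability uniform on 0 to 1; report and prompt use independent. The table gives the mean Spearman correlation of the pooled total with report use.

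| Mean u | 1 reader | 5 readers | 10 readers |
|---|---|---|---|
| 25% | 0.01 | 0.06 | 0.12 |
| 10% | 0.03 | 0.15 | 0.28 |
| 5% | 0.06 | 0.28 | 0.46 |
| 2% | 0.16 | 0.53 | 0.72 |
| 1% | 0.29 | 0.72 | 0.87 |

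With one reader per report, the correlation of the total with prompt use is 0.93 to 1.00 throughout. With ten readers and 1% prompt use it falls to 0.40. Which component the total represents thus depends on two rates that the article does not give.

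**Step 4: the two definitions side by side**

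| | Reports | Decision support tools | Webinars |
|---|---|---|---|
| Process evaluation (compliance) | yes | yes | yes |
| Outcome evaluation (quartiles, trend) | yes | yes | not listed |

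**The case against.** **Tempting stronger reading.** A reader might infer that the 12 reports are always swamped by some 1,867 prompts, so that the usage measures say almost nothing about feedback. The document does not support that. The 1,867 are consultations; an access needs a trigger code and then action by the clinician. Twelve is the number of reports issued, and several prescribers may open each one. At 1–2% prompt use with five or more readers, the total follows report use moderately to strongly (0.53 to 0.87). Engaged practices may also use both components, which would raise the correlation further. This objection stands, and it limits the claim about size.

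**Pooling may not be intended.** In Outcome evaluation, the conjunction between reports and tools, and the plural used when the variables enter the models, could fit a separate count for each component. That reading is possible. One usage variable cut into quartiles is the more natural one, and Process evaluation speaks of a total. If separate counts are meant, one sentence would settle it.

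**The webinar difference may be deliberate.** A short video watched at the start can reasonably count towards compliance and not towards dose. The difference is therefore no clear contradiction, but the text should say so.

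**Other sources cover feedback and the champion.** The planned questionnaire and interviews may inform on both, and the pilot measures list delivery of reports and webinars separately from tool installation. A champion is also not something that is accessed, so absence from an access count is no defect. This stands. It does not repair the quantitative compliance figure or the trend test.

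**This is detail for the SAP.** Had the article been silent, that would hold. It does state what is counted, and that definition is what is questioned.

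**Conclusion.** The point holds for the quantitative usage measures. As written, the compliance total and, on its natural reading, the usage variable for the quartiles and trend test cannot show whether feedback was taken up or is associated with prescribing. This is so at any access rate, because nothing in the sum tells the reader which component drives it.

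The size is conditional. With one reader per report and prompts used in 5% or more of consultations, the total is essentially prompt use (correlation with report use 0.06 or less). Over the whole assumed range, 1–25% prompt use and one to ten readers, that correlation runs from about 0.01 to 0.87. These figures rest on assumed access rates and on independence of report and prompt use.

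The consequence is limited to compliance reporting and a non-randomised secondary analysis. The intention-to-treat comparison of the primary outcome is not affected.

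**What to change.** In Outcome evaluation and Process evaluation, replace the pooled count with two usage variables, defined identically in both places:

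- (a) decision support tool use, as a count of accesses;
- (b) the number of the 12 monthly reports opened at least once by anyone in the practice (0 to 12).

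Run the quartile and trend analysis separately for (a) and (b). Report webinar access on its own as a compliance item. Leave GP champion activity to the planned questionnaire and interviews: these aim for the largest achievable sample of individuals, not every practice, so a champion variable for each practice could not be relied on.

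The cost is wording, a different aggregation of access data that the plan already intends to use, and two trend tests instead of one. It requires that the logs identify the component accessed. Variable (b) still cannot distinguish a report that was discussed from one that was merely opened, and this should be acknowledged when the trend is interpreted.
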